### Strategies to improve adherence to interventions {11c}

To improve adherence to the study protocol, the follow-up visits for the study are planned simultaneously with the standard measurements for patients in the MICS program at the Medical University of Innsbruck. Participants do not need to adhere to specific tasks. To support faculty staff, a study nurse who reviews the patient files throughout the study period will be involved.

### Relevant concomitant care permitted or prohibited during the trial {11d}

There is no expected interaction between the drug under investigation and concomitant medical treatments. Local prescribing information and institutional guidelines should be followed as applicable.

### Provisions for post-trial care {30}

The sponsor has insurance by the legal requirements in Austria. This insurance covers damage to research participants through injury or death caused by the study. The insurance applies to the damage that becomes apparent during the study.

### Outcomes {12}

The primary outcome parameter is the overall opioid demand given as intravenous MME during the first 24 h after extubation.

Secondary outcome variables are the interval until extubation, ICU discharge, data collected in the ICU, length of hospital stay, the VAS at 2, 4, 6, 12, and 24 h after extubation, and the Overall Benefit of Analgesia Score (OBAS) at 24 h after extubation [12].

### Participant timeline {13}

Demographic and baseline data such as age, weight, height, and ASA score are collected soon after informed consent is granted, usually the day before surgery. On the day of surgery, data that define the type of surgery and the type and size of central venous cannulation will be noted. Also, hemodynamic data such as arterial pressure, heart frequency, and blood oxygen saturation before and soon after the performance of the PECS block will be recorded. At the end of the surgery, the amount of opioids and sedatives used during the surgery will be noted. The time of ICU admission and hemodynamic data will be noted at ICU admission.

All opioids and other analgesics will be noted until the extubation and after 2, 4, 6, 8, 12, and 24 h. Also, the NRS score will be assessed at the defined time points.

After 24 h, the OBAS assessment will be performed, and the study participation will end.

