**Methods:**

In a single center, prospective, triple-blinded, two-group randomized trial, 60 patients undergoing elective, unilateral minimal invasive cardiac surgery will be randomized to receive a PECS II with 30 ml of ropivacaine 0.5% (intervention group) or sodium chloride 0.9% (placebo group). The primary outcome parameter is the overall opioid demand given as intravenous morphine milligram equivalents (MME) during the first 24 h after extubation. Secondary endpoints are the visual analog scale (VAS) 2, 4, 6, 8, 12, and 24 h after extubation, the Overall Benefit of Analgesia Score (OBAS) after 24 h, the interval until extubation, and intensive care unit (ICU) discharge within 24 h, as well as the length of hospital stay (LOS).

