### Eligibility criteria {10}

Adult patient with an American Society of Anesthesiologist (ASA) physical status I-III, aged 18–80 years, scheduled for elective minimal invasive cardiac surgery, e.g., mitral valve procedures, tricuspid valve procedures, myxoma resection, or atrial septal defect repair. All participants will undergo the usual standard medical work-up before, during, and after the procedure according to the ESC/EACTS Guidelines on Valvular Heart Disease [14].

This includes echocardiography, spirometry, carotid artery duplex scan, cardiac MRI, and/or computed tomography, and interviews with the cardiologist, cardiac surgeon, and anesthesiologist.

To be eligible for this study, patients must meet all of the following criteria:Age: 18–80 years.BMI 18–35 kg/m.^2^Informed consent.MICS

The exclusion criteria are as follows:Known allergies to administered drugs.Severe diabetic neuropathy.LV-dysfunction (EF < 30%).Drug-opioid abuse.Patients with chronic pain syndrome.Systemic infection.Psychiatric disorders that lead to alteration in the perception and evaluation of pain.Pregnancy.Anticipated endotracheal intubation > 24 h.eGFR < 30 or chronic renal disease.

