### Criteria for discontinuing or modifying allocated interventions {11b}

We will exclude patients from participating in case of failure to detect the suitable anatomical structures for PECS II.

After PECS II is performed, it is impossible to change the allocated intervention after administration. Subjects are free to leave the study at any time for any reason without consequences. Study discontinuation should be documented in the subject’s medical file and the case report form (CRF). The investigator can withdraw an issue from the study for urgent medical reasons. These may include the following criteria:Anatomical anomalies, limited visualizationAllergic reaction to the study medicationClinical complications (hemodynamic impairment, re-operation, extracorporeal membrane oxygenation (ECMO), etc.) that may lead to prolonged weaning (more than 24 h)

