### Methods in analysis to handle protocol non-adherence and any statistical forms to handle missing data {20c}

#### Per-protocol population

The per-protocol-population will include all patients who received intervention or sham intervention (placebo) and surgery without major protocol deviations. Significant protocol deviations or complications (hemodynamic instability, prolonged intubation, reintubation, bleeding, reoperation) and subsequent failure to obtain primary and secondary outcome data will be documented before the database lock.

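### Withdrawal for complications that may prolong weaning, together with the analysis-set and LOCF rules, may remove the longest values of interval to extubation, ICU discharge and length of stay; ICU discharge is also worded in two ways

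*Protocol article*

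**What the plan says.** All references are to the protocol article.

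- **Outcomes {12}:** "Secondary outcome variables are the interval until extubation, ICU discharge, data collected in the ICU, length of hospital stay". Objectives {7} and the outcome list under Study setting {9} also name ICU discharge without a time limit.
- **Abstract, Methods:** the same endpoints are given as "the interval until extubation, and intensive care unit (ICU) discharge within 24 h, as well as the length of hospital stay (LOS".
- **Participant timeline {13}:** "After 24 h, the OBAS assessment will be performed, and the study participation will end". The 24 h run from extubation. The section records the time of ICU admission but names no step for ICU or hospital discharge.
- **Criteria for discontinuing {11b}:** "The investigator can withdraw an issue from the study for urgent medical reasons". One listed criterion is clinical complications "that may lead to prolonged weaning (more than 24 h".
- **Per-protocol population, under {20c}:** "Significant protocol deviations or complications (hemodynamic instability, prolonged intubation, reintubation, bleeding, reoperation") and any resulting failure to obtain outcome data are to be documented before database lock.
- **Intention-to-treat population, under {20c}:** this consists of enrolled, consented patients whose data are missing because of those factors. It is analysed as a separate cohort, with LOCF where appropriate.
- **Plans for assessment {18a}:** healthcare data are taken from the electronic patient file.

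**The concern.** Interval to extubation is an outcome, and a reason for leaving the study after randomisation is a complication expected to make that interval long. Patients who leave this way are likely to have the longest ventilation times, and probably the longest ICU and hospital stays.

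If the block has no effect on weaning and withdrawal is blind to arm, removing these patients mainly narrows the population described. If the block does shorten weaning, more patients leave the slower arm and the estimated difference shrinks. The Introduction and Discussion give prolonged ventilation, ICU stay and hospital stay as part of the enhanced-recovery rationale, so the upper tail matters for interpretation.

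Separately, ICU discharge within 24 h reads as a yes/no outcome, whereas ICU discharge without a limit reads as a time. The two need different analyses. The unlimited version, like length of stay, can fall after the stated end of participation.

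**Working it through.** **1. The plan's own figure.** The only calculation in the document is the primary-outcome sample size. With d = 0.75, 80% power and 5% two-sided (sidedness is not stated; two-sided is assumed), the normal approximation gives n = 2 × (1.960 + 0.842)² / 0.75² = 27.9, so 28 per group as stated. This point does not change it. The plan gives no figure for the secondary outcomes.

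**2. Who remains in the analysis of interval to extubation?**

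| Patient | Per-protocol set | Intention-to-treat set | Value available |
|---|---|---|---|
| Extubated, data complete, no major deviation | Yes | Not by the wording, which describes patients with missing data | Yes |
| Prolonged intubation, not withdrawn | Unclear: the event is documented, exclusion is not stated | Only if data are missing | Yes |
| Withdrawn for a complication that may prolong weaning | Unclear, and data probably missing | Yes, as a separate cohort | None before extubation |

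Neither set is defined as all randomised patients, by randomised group, with the observed value.

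**3. Does LOCF fill the gap?** LOCF needs an earlier measurement of the same variable. The repeated pain scores have one. Interval to extubation, time to ICU discharge and length of stay are each a single number per patient, so there is nothing to carry. If LOCF is judged not appropriate here, the article gives no other rule for these outcomes.

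**4. What does the 24 h end of participation affect?** The clock starts at extubation, so interval to extubation is already complete. Length of stay, and ICU discharge if unlimited, can be reached later.

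**5. Size of the selection, under assumptions.** The documents give no distribution of extubation times. Assume they are lognormal with control median m, log-SD s and treated median 0.8m, and that every patient not extubated by 24 h is removed. With Φ the standard normal distribution function and a = (ln 24 − ln m)/s:

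- share removed = 1 − Φ(a)
- full mean = m × exp(s²/2)
- mean after removal = full mean × Φ(a − s)/Φ(a)

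Example, m = 12 h and s = 1.0:

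- Control: a = 0.693; full mean 19.79 h; after removal 19.79 × 0.3795/0.7559 = 9.93 h.
- Treated (median 9.6 h): a = 0.916; full mean 15.83 h; after removal 15.83 × 0.4666/0.8202 = 9.00 h.
- The difference falls from 3.96 h to 0.93 h.

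| m (h) | s | Removed, control | Removed, treated | Difference, all (h) | Difference after removal (h) |
|---|---|---|---|---|---|
| 6 | 0.5 | 0.3% | 0.1% | 1.36 | 1.31 |
| 6 | 1.0 | 8.3% | 5.4% | 1.98 | 0.92 |
| 8 | 0.8 | 8.5% | 4.9% | 2.20 | 1.19 |
| 12 | 0.5 | 8.3% | 3.3% | 2.72 | 1.82 |
| 12 | 1.0 | 24.4% | 18.0% | 3.96 | 0.93 |

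In patients: if 3% to 10% exceed 24 h (assumed), that is 60 × 0.03 = 1.8 to 60 × 0.10 = 6 of 60.

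**The case against.** The case for leaving the text alone has several sound parts.

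- **Withdrawal is neither automatic nor triggered by the outcome value.** It is at the investigator's discretion, for urgent reasons, and rests on a complication. A patient who weans slowly without one is not covered. Staff are blinded. Eligibility {10} already excludes "Anticipated endotracheal intubation > 24 h", which acts before randomisation and introduces no bias. All this stands. It makes the loss smaller and less certain, but selection related to the outcome remains possible.
- **The per-protocol section says the listed events are documented, not that they are excluded.** This stands. A reader might infer that prolonged intubation is a stated exclusion; the text does not go that far, but it leaves the handling open.
- **Length of stay can be retrieved.** A reader might infer from the timeline that it cannot be obtained. The patient file is a named source, a study nurse reviews it, and the end of participation may mean only the last assessment. This stands, and on its own the missing collection step is close to detail left to the full protocol.
- **Withdrawn patients' data may be used.** The consent provisions {26b} ask this of participants who choose to withdraw. They do not expressly cover withdrawal by the investigator, so this answers only part of the point.
- **The large bias needs many long ventilations.** This is correct: about a quarter of controls in the most severe row. Nor would a 10% versus 3% contrast be lost because of these rules: it is about 3 versus 1 of 30, with a two-sided Fisher p of about 0.61 even with complete data.

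A preference for a competing-risk model would be an analysis choice, not a defect of the plan.

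**Conclusion.** The point holds in a limited form. Taken together, the withdrawal criterion, the two population definitions and LOCF leave no set that clearly retains all randomised patients for interval to extubation, ICU discharge and length of stay, and the values at risk are the longest ones. The effect runs from negligible (1.36 to 1.31 h) to severe (3.96 to 0.93 h). This range rests on the assumed lognormal shape, a 20% effect and removal of every patient beyond 24 h, which is stricter than the discretionary rule. The documents do not show where in that range the trial lies.

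The two wordings of ICU discharge are a plain contradiction. The end of participation needs a clarifying sentence.

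Two stronger readings are not supported. The end of participation does not cut off interval to extubation, because extubation comes before the 24 h window. An effect on delayed extubation is not removed by design; it may be attenuated if eligible withdrawals are made and their data are not kept. Only secondary outcomes are addressed here.

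**What to change.** 1. State that leaving the study procedures does not end data collection. Extubation, ICU discharge and hospital discharge times are recorded for all randomised patients, including those with prolonged weaning, subject to consent. The clinical decision to withdraw is not at issue here.
2. Analyse these three outcomes in all randomised patients by randomised group. Use a rank-based or time-to-event method that retains long values, and do not use LOCF or removal for them.
3. Use one definition of ICU discharge throughout, either yes/no within a stated window with its starting point, or a time.
4. Add to the timeline that ICU and hospital discharge dates are read from the patient file up to discharge.
5. Reconcile the abstract, Objectives {7}, Study setting {9}, {11b}, Outcomes {12}, Participant timeline {13} and the two population definitions under {20c}.

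The cost is wording, a few extra dates per patient from a source already in use, and a check that the consent covers routine data to discharge and withdrawal by the investigator. If the ethics committee treats the change as substantial, a formal amendment is needed. No extra patients or visits are required.

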### Sample size {14}

The main hypothesis of this study is that the use of PECS II blockade in patients undergoing minimally invasive cardiac surgery reduces the overall opioid demand given as morphine milligram equivalents (MME) during the first 24 h after extubation. The sample size needed to test this hypothesis was based on four previous studies [15–18]. Study results were pooled and weighted due to considerable heterogeneity in variances. Assuming an average weighted effect size of 0.75 (Cohen’s *d*) aiming for a statistical power of 80% and a testing significance level of 5%, a sample size of 28 patients per group is required. Considering a potential dropout rate of 7%, we enrolled 60 patients (30 patients per group).

### Recruitment {15}

The MICS program at the University Clinic of Cardiac Surgery, Medical University of Innsbruck, serves as the primary recruitment institution.

## Assignment of interventions: allocation

### Sequence generation {16a}

The investigational medication (ropivacaine 0.5%) assigned to individual patients is determined by a randomized schedule with a 1:1 allocation ratio.

### Concealment mechanism {16b}

The randomization process will be realized independently from the clinical investigators using opaque envelopes (fully blind randomization). For each participant enrolled in the study, one envelope will be opened by the nurse who prepares the study medication. Preparation will be performed in a separate room without the attendance of any study investigator.

### Implementation {16c}

The randomization list will be generated using well-established software (randomization.org) for the two groups (intervention group, placebo group). Upon the arrival of the patient in the operating theatre, a study nurse will open an opaque envelope which is labeled with the patient’s identification code and prepare the study medication (30 ml ropivacaine 0.5% for the intervention group and 30 ml sodium chloride 0.9% for the placebo group) according to the study randomization and hand it to the blinded anesthetist.

## Assignment of interventions: blinding

### Who will be blinded {17a}

This study is, per definition, triple-blinded as the participants, care providers, and investigators involved in the study procedure do not know the randomization arm. All study assessments will be performed in an observer-blinded fashion.

### Procedure for unblinding if needed {17b}

A patient identification code will replace patient identifying data. The randomization list and the codebook will be stored digitally and only accessible to study personnel. Unblinding is possible at all times after consultation with the principal investigator.

## Data collection and management

### Plans for assessment and collection of outcomes {18a}

All investigators will be trained within the initiation visit. Training topics cover Good Clinical Practice, the study protocol, and OBAS and VAS assessment execution.

The patient’s demographical data will be registered soon after the patient’s informed consent. The PECS II block will be performed by experienced anesthesiologists who have completed at least 50 procedures. All data will be collected using a paper-based CRF. The healthcare data of participants will be derived from the electronic patient file. All data will be stored for 15 years, and results will be published in scientific journals.

### Plans to promote participant retention and complete follow-up {18b}

After enrollment and randomization, the investigators will make every reasonable effort to follow the study subject throughout the entire study period. Subjects are free to discontinue their study participation at any time. Participant retention will be increased by implementing study visits into routine clinical postoperative care.

### Data management {19}

An independent internal monitor (Tirol Kliniken) will provide the monitoring and quality assurance of the study. The study team will process data entry from paper based CRF into statistical software. Programmed checks make data validation of range, validity, and consistency. If necessary, queries are made by the study software or an authorized person. Based on the questions, the investigator can check and clarify discrepancies.

After recording all entries and clarifying all queries, the database will be closed after the study. This performance must be documented. All data will be handled confidentially, and research data will be coded using a unique patient identification number. To reproduce the study findings and help future users understand and reuse the data, all changes made to the raw data and all steps taken in the analysis will be documented. The database files will be kept for 15 years after the study has ended.

### Confidentiality {27}

All local legal requirements regarding data protection will be adhered to. All study findings and documents will be regarded as confidential. The Investigator and research team members must not disclose any information without prior written approval from the Sponsor.

The pseudonymity of patients participating must be maintained. The patients will be recognized on CRFs and other documents by age and identification number throughout documentation and evaluation. Records that identify the patient personally (e.g., the signed informed consent) must be maintained in confidence by the investigator. The patients will be told that all study findings will be stored on a computer and handled in the strictest confidence.

### Plans for collection, laboratory evaluation, and storage of biological specimens for genetic or molecular analysis in this trial/future use {33}

Not applicable; no biological specimens will be collected for this study.

## Statistical methods

### Statistical methods for primary and secondary outcomes {20a}

Data will be entered into electronic case record files (eCRF; RedCap®, Nashville, TN). R 4.2 (The R Project for Statistical Computing, Vienna, Austria) will be used for statistical analysis. The normality of data will be assessed using graphical and inferential tests. Median/interquartile range or mean/standard deviation will be used to summarize and evaluate continuous data and count/percent for categorical data. Student’s *t*-test and *χ*2 or non-parametric equivalents will be used for intergroup distribution comparisons at defined time points. For repeated measures, analysis of variance (rmANOVA) and generalized linear models (generalized estimating equation (GEE)) will be used. Linear and/or logistic regression will be used to estimate intervention effects on primary and/or secondary outcomes, controlling for common confounding factors and effect modifiers.

### Interim analyses {21b}

This study can be classified as low risk; no interim analyses will be conducted during this trial.

### Methods for additional analyses (e.g., subgroup analyses) {20b}

No subgroup analysis is planned, justified by the sample size and the pragmatic study design.

We anticipated that there would be meaningful differences in treatment effects across subgroups of participants.

### Sample size

Our study was designed to detect an effect of the PECS II block on 24 h postoperative opioid demand. As patients undergoing minimal invasive mitral valve surgery tend to be quite a homogenous population, to our understanding, conducting subgroup analyses would not have added much value to our study. Also, conducting subgroup analyses would have reduced our statistical power. Therefore, we were concerned that subgroup analyses would not yield meaningful results.

### Methods in analysis to handle protocol non-adherence and any statistical forms to handle missing data {20c}

#### Per-protocol population

The per-protocol-population will include all patients who received intervention or sham intervention (placebo) and surgery without major protocol deviations. Significant protocol deviations or complications (hemodynamic instability, prolonged intubation, reintubation, bleeding, reoperation) and subsequent failure to obtain primary and secondary outcome data will be documented before the database lock.

#### Intention-to-treat population

The intention-to-treat population will consist of all patients who were enrolled in the study and gave informed consent, but data is missing due to the abovementioned factors. This population will be analyzed in a separate ITT cohort. In case of withdrawals and missing data, the last observation carried forward (LOCF) procedure will be applied where appropriate.

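### The intention-to-treat population is defined as enrolled patients whose data are missing, so no stated analysis compares all randomised patients in their assigned arm

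*Protocol article*

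**What the plan says.** Section {20c} of the Protocol article sets out two analysis populations.

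- **Per-protocol population:** "all patients who received intervention or sham intervention (placebo) and surgery without major protocol deviations". The next sentence names "Significant protocol deviations or complications (hemodynamic instability, prolonged intubation, reintubation, bleeding, reoperation" and says that these, together with a resulting failure to obtain outcome data, are to be documented before database lock.
- **Intention-to-treat population:** "all patients who were enrolled in the study and gave informed consent, but data is missing due to the abovementioned factors". It continues: "This population will be analyzed in a separate ITT cohort". For withdrawals and missing data, "the last observation carried forward (LOCF) procedure will be applied where appropriate".

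Two provisions in Criteria for discontinuing or modifying allocated interventions {11b} also decide who remains. One concerns anatomy: "We will exclude patients from participating in case of failure to detect the suitable anatomical structures for PECS II". The other lets the investigator withdraw a patient for urgent medical reasons, including clinical complications "that may lead to prolonged weaning (more than 24 h").

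The primary outcome (Outcomes {12}) is the total intravenous morphine equivalent over the 24 h after extubation. Statistical methods {20a} does not tie its tests or regressions to either population.

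**The concern.** An intention-to-treat set should hold everyone randomised, in the arm assigned, whatever happened afterwards. Here the label is given to the patients whose data are missing because of deviations or complications, and they are set apart from the rest. Taken at its word, this set cannot carry the primary comparison, and the set that remains is selected on what happened after allocation.

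The envelope is opened before the patient arrives in theatre ({11a}) or on arrival ({16c}), in either case before the block. Bleeding, reoperation, reintubation and prolonged intubation come later. They can plausibly relate both to opioid use and to the time of extubation, which starts the 24 h outcome window. If such patients leave the analysis unevenly by arm, the difference in opioid demand no longer rests on randomisation alone.

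**Working it through.** **1. The plan's own sample size.** Inputs from Sample size {14}: d = 0.75, power 80%, significance level 5% (sidedness not stated; two-sided reproduces the figure), dropout 7%.

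- n per arm = 2(1.960 + 0.842)² / 0.75² = 27.9, so 28. This matches. The exact t-test gives 28.9, so 29.
- 28 × 1.07 = 30.0, so 30 per arm and 60 in total. This matches. Dividing instead, 28 / 0.93 = 30.1, gives 31.

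The calculation therefore expects all but about 4 of the 60 patients to be in the main comparison.

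**2. Size of the literal intention-to-treat cohort.** 60 × 0.07 = 4.2, about 4 patients or 2 per arm. Even if their data were complete, t-test power at d = 0.75 with 2 per arm would be about 8%.

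**3. Is there another set of all randomised patients?** Reading the sections together:

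- Per-protocol requires block and surgery without major deviations, so it is not everyone randomised.
- Intention-to-treat requires missing data from the listed factors, so it is not everyone randomised either.
- {20a} applies its methods to no named set.
- {20b} and the Sample size paragraph that follows it deal only with subgroups.

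No section defines all randomised patients analysed as assigned.

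**4. Possible bias of a per-protocol comparison.** Let p be the proportion excluded in an arm and h the excess opioid use of excluded over retained patients, in SD, the same in both arms. The arm's full mean is the retained mean plus p·h. Hence

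bias of the per-protocol difference = (difference in p between arms) × h.

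The document gives neither p nor h. Assuming 20% against 10%, and h between 0.5 and 1:

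- 0.10 × 0.5 = 0.05 SD, and 0.05 / 0.75 = 7% of the planned effect.
- 0.10 × 1.0 = 0.10 SD, and 0.10 / 0.75 = 13% of the planned effect.

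If the control arm loses more high users, the benefit is understated. If the active arm does, it is overstated. The signs reverse if excluded patients use less opioid.

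**5. A wider range.** Now let excluded patients lie s = 1 SD above their arm's full mean, with no true effect and 30 randomised per arm. The bias is p₁s/(1 − p₁) − p₂s/(1 − p₂). Type I error is simulated with 20,000 trials.

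| Excluded, arm 1 / arm 2 | Bias (SD) | Type I error |
|---|---|---|
| 7% / 7% | 0 | 0.049 |
| 10% / 3.3% | 0.08 | 0.057 |
| 13.3% / 0% | 0.15 | 0.089 |
| 20% / 6.7% | 0.18 | 0.097 |

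All these rates are assumptions. Balanced exclusion does no harm in this model; imbalance does.

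**6. Does the carry-forward rule repair the set?** The outcome is a cumulative total. If a record stops at 12 h and the running total is carried forward, use from 12 to 24 h is counted as zero. At a constant rate of use (assumption) that keeps 12/24 = 50% of the true total. For a patient never extubated, the window never opens and there is nothing to carry forward.

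**The case against.** The best defence is that this is loose English: the authors meant all enrolled patients, including those with missing data, analysed separately from per-protocol. The article has other evident slips, so the intention may well have been sound. But the printed definition restricts the set to missing data and then calls it separate. An unseen analysis plan does not cure a wrong definition stated here.

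Several stronger readings are tempting and are not supported:

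- **That the set includes people never allocated, because consent comes earlier.** Baseline data are "collected soon after informed consent is granted, usually the day before surgery", so consent does precede the envelope. But the definition also requires enrolment, and Concealment mechanism {16b} ties each enrolled participant to an opened envelope. {18b} does list enrolment and randomisation as two steps, so the point is at most ambiguous.
- **That complications are an explicit per-protocol exclusion.** The text says they are documented. Exclusion is inferred from the bar on major deviations, the separate cohort and the withdrawals in {11b}.
- **That only per-protocol patients have outcome data.** Participant timeline {13} records opioids until extubation and then at set times to 24 h, so patients outside per-protocol may have full or partial totals. For the same reason, an as-randomised analysis is feasible; it is simply not defined.
- **That power falls materially below 80% because of this.** The t-test gives 78.7% at the plan's own 28 per arm. At 27 it is 77.2%, and at 24 (20% exclusion, assumed) 72.0%. The fair comparison is with 78.7%, and the loss depends on an assumed rate.
- **That failing to name a primary population is itself an error.** A condensed article may leave that to the full documents.

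It also stands that the illustrative bias is modest: 0.05 to 0.10 SD, against a standard error of √(1/24 + 1/27) = 0.28 SD.

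**Conclusion.** The concern holds, confined to the definition. As printed, the intention-to-treat population is roughly the complement of per-protocol, about 4 of 60 patients at the planned dropout, and no section defines a comparison of all randomised patients as assigned. That conclusion rests on the wording alone and needs no assumption beyond the plan's own 7%.

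The consequence for the result is less certain. A per-protocol comparison could be biased in either direction. The figures of 0.05 to 0.10 SD (7 to 13% of the planned effect), and the larger values under stronger imbalance, rest on assumed exclusion rates and assumed excess opioid use. If exclusions are few and balanced, the bias is negligible, but the stated plan contains no analysis that would show this. The definition should be corrected before database lock because it decides who is counted in the primary comparison.

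**What to change.** Reword the Intention-to-treat population section along these lines: *The intention-to-treat population is all randomised patients, analysed in the arm assigned, regardless of complications, reintubation or reoperation. It is the primary analysis set. The per-protocol analysis is a sensitivity analysis.* One exception may be allowed: patients excluded for unsuitable anatomy before any injection, with the decision made blind to allocation.

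The carry-forward rule sits in the same section, so it needs a replacement and not mere deletion. For the primary outcome, use the opioid records already collected through 24 h, including those of patients with complications. Where the 24 h total is incomplete, or the patient is never extubated, state in advance how the patient is handled, for example by multiple imputation with a sensitivity analysis.

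The cost is a wording change and a little more analysis work. No new data collection or sample size is needed: with all 30 per arm analysed, t-test power at d = 0.75 is 81.5%, and 78.7% with 28. The price is a slightly more variable outcome, since patients with complicated courses stay in, so those power figures could be a little optimistic.
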